## Abstract

**Background:**

Onychomycosis is a common fungal nail disease with a prevalence rate up to 14% in North America and 24% in Europe. The current treatment paradigm is limited by a high risk of disease recurrence, safety concerns for oral agents, and a low likelihood of patients achieving both clinical improvement and mycological cure. Recent advances in device‐based treatments have allowed for the direct targeting of the infection site that bypasses drug resistance mechanisms while minimizing systemic side‐effects. The Swift^®^ System is a microwave device that has demonstrated therapeutic potential in treating skin (e.g. verrucae vulgaris, actinic keratosis) and nail infections.

**Methods:**

We report the protocol of an open‐label, randomized, pilot study that will be conducted at a single Canadian center. Our primary objective is to evaluate the safety and efficacy of microwave treatment (Swift^®^ System, Emblation Ltd, Scotland, U.K.), administered at three different dosing regimens, in 45 patients with mild‐to‐moderate distal subungual onychomycosis. Our secondary objective is to identify an optimal dosing regimen, if any, to better inform the conduct of a future pivotal trial. Patients will be randomized (1:1:1) to undergo either 9 treatment sessions (5 weekly sessions plus 4 monthly sessions), 7 treatment sessions (3 sessions every 2 weeks plus 4 monthly sessions), or 12 treatment sessions every 2 weeks. At each session microwave energy will be applied in 3‐s intervals at 7–9 Watts, repeated up to 5 times at each treatment position on the nail. Overlapping treatment positions are used to ensure sufficient coverage of the infected area. Patients will be enrolled in the trial over a 12‐month period. Efficacy will be evaluated based on visual improvement and mycology testing results. Adverse events will be recorded throughout the entire study period.

**Discussion:**

This study will be the first to report on the safety and efficacy of microwave treatment in onychomycosis patients in a trial setting; recruitment is ongoing.

**Trial registration:**

ClinicalTrials.gov, NCT05674747.

## BACKGROUND

1

Onychomycosis, or tinea unguium, is the most common cause of nail disorders worldwide accounting for at least half of nail dystrophies seen in the clinic.^1^ This chronic, slow‐progressive, fungal nail disease is more prevalent among the elderly and in individuals living with diabetes and peripheral vascular disease.^1^, ^2^ Clinical manifestations include nail thickening, brittleness, discolouration and nail plate separation (onycholysis), which may be accompanied by localised pain and numbness impairing ambulation.^1^

The most common presentation of onychomycosis is infection that originates at the hyponychium or the lateral nail fold which then progresses proximally invading the stratum corneum of the nail bed,^3^ known as distal subungual onychomycosis (DSO). Dermatophytes, a group of filamentous fungi with the ability to degrade keratin, are frequently identified as the causative organisms in onychomycosis patients; in particular, *Trichophyton* (i.e., *T*. *rubrum* and *T*. *mentagrophytes*) is the predominant dermatophyte found in North America.^4^

Although several topical and oral treatment options exist,^5^ there remains an unmet need for treatment that achieves both clinical and mycological cure (i.e., normal‐appearing nail with the complete eradication of the underlying fungal infection) and treatment that reduces the risk of disease recurrence. Device‐based treatments, such as lasers, photodynamic therapies and microwaves, offer a promising potential in directly targeting the site of infection with minimal systemic side‐effects risk.^6^ Furthermore, device‐based modes of treatment can bypass dermatophyte antifungal resistance mechanisms towards oral and topical agents (e.g., terbinafine) as recently reported.^7^, ^8^ Despite these advantages, clinical reports available for devices remain limited other than lasers where high‐quality data and results are still inconsistent. The absence of conclusive data for any single treatment to date highlights the need for broadening the medical armamentarium to address all the challenges posed by onychomycosis.

Microwaves as a treatment modality for fungal infections offer potential as a unique approach as they use water within the tissue to generate heat. Microwaves do not generate heat the way lasers do—by direct absorption of photons. Instead, microwaves create rapidly oscillating electric fields that cause water, ions and other small polar molecules to rotate or move, which in turn generates heat. This means that microwaves can have good penetration, are non‐ionizing (i.e., do not damage proteins and DNA directly), and still can rapidly heat tissues. This permits rapid heating of infected nail plates, even if dystrophic nails are thick and opaque. Lasers, in contrast, rely on thermal diffusion of heat generated at the nail surface to reach dermatophytes in and below the nail plate.

Microwave treatment, through its multimodal mechanisms of action, has previously demonstrated antifungal effects in vitro.^6^ In addition to locally induced hyperthermia leading to protein denaturation and fungal cell death, microwave energy may disrupt the ability of dermatophytes to evade natural defence mechanisms and immune responses of the nail.^6^, ^9^ Previous studies have demonstrated favourable efficacy of the Swift^®^ microwave device in patients with plantar warts, including in patients with multiple prior failed treatments and warts lasting for ≥2 years^10^, ^11^ In a case report, a patient presenting with onychomycosis complicated by dermatophytoma (i.e., compacted fungal elements recalcitrant to treatment) demonstrated significant clinical improvement after undergoing six treatment sessions.^12^

The Swift^®^ System is a microwave device that has been cleared by the US FDA (510(k) number: K181941), Health Canada for general dermatology and podiatry use (licence number: 98352) and is CE (Conformité Européenne) marked, allowing it to be sold within the European Union in compliance with European medical device regulations. In this trial, we sought to evaluate the safety and efficacy of the Swift^®^ microwave treatment, administered at three different dosing regimens, in Canadian patients with mild‐to‐moderate onychomycosis. To our knowledge, the present trial is the first to evaluate the safety and efficacy of microwave treatment in onychomycosis patients, utilising both the US FDA recommended endpoint and mycological testing.

## METHODS/DESIGN

2

In this open‐label, randomized, pilot study, we aim to evaluate the safety and efficacy of microwave treatment (Swift^®^ System, Emblation Ltd.) for mild‐to‐moderate onychomycosis at a single Canadian dermatology clinic (Mediprobe Research Inc.). A total of 45 subjects will be enroled into the study and efficacy will be evaluated primarily based on the ‘temporary increase of clear nail’ in accordance with the US FDA recommendation.^13^ Our secondary objective is to identify an optimal dosing frequency, if any, to better inform the conduct and design of a pivotal trial.

This pilot trial has been prospectively registered with ClinicalTrials.gov in January, 2023 (NCT05674747). The trial protocol, recruitment material and consent form has received Institutional Review Board (IRB) approval (Advarra, Inc., protocol number: FN1p, version: amendment 1, date: 19 May 2023). The trial will be conducted in adherence to the International Conference on Harmonisation Good Clinical Practice (ICH GCP) and the International Organisation for Standardisation (ISO) Clinical Investigation of Medical Devices on Human Subjects‐Good Clinical Practice; local and national regulations including the Health Canada Medical Device Regulations will be followed. Any changes in study design will require formal protocol amendments approved by Advarra IRB. The principal investigator is primarily responsible for the design and conduct of the trial, preparations of the study protocols including amendments and managing the trial site. The support service personnel will prepare case report forms and conduct imaging analyses and statistical analyses. Reporting of the trial protocol herein follows the recommendation by Thabane and Lancaster^14^ and is in accordance with SPIRIT (Standard Protocol Items: Recommendations for Interventional Trials) guideline.^15^, ^16^

### Study participants

2.1

Adult patients presenting with DSO of one hallux, with 20%–75% involvements of the nail area, nail thickness of ≤3 mm and no area of infection <3 mm from the proximal nail fold, will be enroled and allocated to treatment. Inclusion and exclusion criteria are summarised in Table 1. No eligibility waivers will be permitted.

**TABLE 1 ski2455-tbl-0001:** Patient eligibility criteria.

Inclusion criteria
Provide written informed consent Aged ≥18 years Not pregnant or breastfeeding Subject presenting with distal subungual onychomycosis of one hallux Mycology‐positive diagnosis confirmed by the detection of a dermatophyte One hallux as a treatment target with 20%–75% nail area affected One hallux as a treatment target with a thickness of ≤3 mm No area of infection <3 mm from the proximal nail fold No more than 4 toenails showing visual signs of onychomycosis including the treatment target Subject agrees not to take any oral or topical antifungal treatments for the duration of the study Subject able to undergo study assessments

Exclusion criteria
Subject presenting with proximal subungual onychomycosis or superficial white onychomycosis Hallux designed as the treatment target shows disease involvement of the lunula Non‐onychomycotic dystrophy presenting as parallel lines, small pinpoint depressions, brown spots, black or brown linear streaks, complete yellowing of all nails without textual changes, green debris below the nail or notches in the nail margin Causative fungal agent belonging to rare species or non‐fungal organisms such as non‐dermatophyte mould, *Candida*, or bacteria ‘Spike’ of onychomycosis extending to <3 mm away from the eponychium Presence of dermatophytoma Type I or II diabetes mellitus Peripheral vascular disease Recurrent cellulitis Lymphatic insufficiency Immunocompromised Severe moccasin tinea pedis Any uncontrolled condition which, in the opinion of the investigator, may put the subjects at undue risk of adverse effects during the study Exhibit an increased risk of bacterial infections due to skin breakdown caused by a fungus Co‐morbidities known to induce nail changes including psoriasis and lichen planus Trauma due to ill‐fitting shoes, running or overly‐aggressive nail care Regularly scheduled podiatric/nursing nail care History of recent toenail surgery with residual disfigurement Recent topical onychomycosis treatments ≥3 months prior to study treatment or oral onychomycosis treatments ≥6 months prior to study treatment Implantable cardioverter defibrillator, pacemaker or other implantable devices Metal implants at or near the treatment site History of intolerance or allergy to microwave therapy History of any topical metallic or ionic treatment within the last 6 months Current participation of another non‐observational trial or within the last 30 days

Patients will be evaluated at enrolment, which includes medical history, concomitant medications (prescriptions, over‐the‐counter medications, supplements), onychomycosis disease duration and treatment history, and toenail measurements (i.e. nail thickness, total affected nail surface area and lowest distance between the affected nail area to the proximal nail fold) (Figure 1); Flyers/posters, online and radio advertisements will be used to increase enrolment. Once a patient provides written informed consent and meets the eligibility criteria, one affected hallux will be sampled for mycology testing (i.e., fungal culture, polymerase chain reaction [PCR] and direct potassium hydroxide [KOH] microscopy). Patients testing PCR and/or fungal culture positive for dermatophytes will be eligible to join the study.

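### The exclusion for earlier onychomycosis treatment contradicts itself: its inequality signs run against the word Recent, and no other text states a pre-study washout

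*Protocol article*

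**What the plan says.** Section 2.1 of the protocol article summarises eligibility in Table 1. Under the heading for "exclusion criteria" the table gives "Recent topical onychomycosis treatments ≥3 months prior to study treatment or oral onychomycosis treatments ≥6 months prior to study treatment".

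Four other places bear on how this should be read:

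- Two further look-back exclusions in the same list are worded the other way. One is "History of any topical metallic or ionic treatment within the last 6 months". The other concerns participation in another trial, currently "or within the last 30 days".
- The inclusion list has "Subject agrees not to take any oral or topical antifungal treatments for the duration of the study". This covers the study period and not the time before it.
- At enrolment the site records "onychomycosis disease duration and treatment history", with no time window attached (section 2.1).
- Section 2.1 adds "No eligibility waivers will be permitted".

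**The concern.** A washout exclusion is meant to keep out patients whose nails may still be responding to an earlier drug. With the signs as printed, the criterion points the opposite way from its first word.

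The direction matters in this trial for three reasons:

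- All three groups receive the microwave device (section 2.2). No untreated or sham group exists against which a residual drug effect would show up.
- The month-3 co-primary efficacy criterion is met by an increase in clear nail length or area, and no minimum is stated (section 2.5). A small residual effect could therefore count as a response. The month-6 clear-nail criteria and the mycological and effective cure endpoints (section 2.6) are open to the same effect.
- The groups are compared by Chi-square test (section 2.8) to inform a pivotal trial (section 2). With arms this small, a few misattributed responses in one group would affect that comparison.

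**Working it through.** The document gives no figure to reproduce. The check is a reading of the rule, followed by one illustrative calculation.

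**Step 1: apply the inequality as printed.** Let t be the time in months from the last onychomycosis treatment to study treatment. The rule excludes a patient if t(topical) ≥ 3 or t(oral) ≥ 6.

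| Patient | Test | Result by the inequality alone |
|---|---|---|
| Topical, 1 month before | 1 ≥ 3 is false | not excluded |
| Topical, 12 months before | 12 ≥ 3 is true | excluded |
| Oral, 2 months before | 2 ≥ 6 is false | not excluded |
| Oral, 24 months before | 24 ≥ 6 is true | excluded |
| Never treated | no t | not excluded |

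Every treated case comes out opposite to what *Recent* implies.

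**Step 2: look for a reading that removes the conflict.**

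- As a required treatment-free interval, the signs would make sense in an inclusion list. The item stands in the exclusion list.
- A fault in reading the PDF is unlikely. The opposite sign comes through correctly in the same table, in "One hallux as a treatment target with a thickness of ≤3 mm", and the minimum age of 18 years carries a correct ≥.
- The neighbouring exclusions quoted above both bar recent exposure, which agrees with *Recent* and not with the signs.

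**Step 3: look for a washout elsewhere.** There is none. The inclusion item covers antifungals during the study, and the enrolment assessment records earlier treatment without setting a limit on it.

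**Step 4: scale, as an illustration only.** Inputs: 39 patients enrolled (section 4), and an even split over three groups, which is an assumption because the article does not give the numbers per arm.

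- Patients per arm: 39/3 = 13.
- One response due only to carry-over adds 1/13 = 7.7 points to that arm's rate and 1/39 = 2.6 points to the pooled rate.
- In an analysis that drops that patient, an arm with k responders moves from k/13 to (k − 1)/12, a difference of (13 − k)/156. For k = 1 this is 12/156 = 7.7 points. For k = 5 it is 38.5% − 33.3%, or 8/156 = 5.1 points.

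So 7.7 points per patient is a ceiling for the with-and-without comparison. It reflects the small arms and is not evidence that any such patient was enrolled.

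**The case against.** The strongest reply is that this is a slip in a journal table with no consequence for the trial. Table 1 is described as a summary. The operative text is the IRB-approved protocol (amendment 1, section 2), which is not shown. There is a single site, and the principal investigator there is also responsible for preparing the protocol. Enrolment was complete by May 2024 (section 4), so the article's wording need not have governed who was enrolled. The word *Recent* and the parallel exclusions make the intent plain enough that a clinician would be unlikely to apply the reversed rule. Patients also had to be dermatophyte-positive by PCR and/or culture with 20%–75% of the nail affected, and concomitant medications and treatment history were recorded. These safeguards limit carry-over and make a breach detectable.

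Most of this stands. A reader might infer from the ban on waivers that the site must have enrolled recently treated patients and turned away those already washed out. The document does not support that. The ban binds the site to the protocol's criteria and does not show that the protocol contains the same error. Nor is the sentence a coherent reversed rule: treatment years ago is not recent, so the text contradicts itself. A reader might also multiply 7.7 points by some number of affected patients and treat the product as the bias, but the document gives no such number.

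The reply does not remove the error. The article states the criterion, states it wrongly, and gives no correct version elsewhere. A positive baseline test and a recorded history do not rule out residual drug effect.

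**Conclusion.** The point holds as an error in a stated eligibility rule. The direction of the inequality contradicts the criterion's own wording and the other look-back exclusions, and the article has no other pre-study washout. As published, the rule misdescribes the intended population and would mislead anyone who reuses it for the pivotal trial.

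Bias in the trial's results is not shown. Whether the approved protocol has the same wording, and whether the site applied it, cannot be judged from this document. The size of any effect is unknown. The only figure available is the ceiling of 7.7 points per carry-over responder in one arm, which rests on the assumed 13 patients per arm.

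The check is still worth making before efficacy results are reported. The endpoints have no untreated comparator, so carry-over could not be recognised from the results themselves.

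**What to change.** 1. Compare the Table 1 item with the IRB-approved protocol. Reconcile it with *Recent* and with the parallel exclusions, and correct the direction of the inequality. The document's own 3- and 6-month figures stay as they are; no other washout length is proposed here.
2. Because enrolment is closed, check the treatment history recorded at enrolment for every enrolled patient. Identify anyone given topical treatment inside the 3-month window or oral treatment inside the 6-month window before study treatment. The trial is open-label, so do this without reference to response.
3. If anyone is identified, report the primary efficacy endpoint with and without those patients, by group and pooled. If no one is, one sentence saying so closes the matter.

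The cost is a one-line correction, a review of 39 histories already collected and at most one extra table. The drawback is that some patients may be flagged as outside the intended criteria, which would have to be reported. Steps 2 and 3 are a check and not a remedy for proven bias.

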**FIGURE 1 ski2455-fig-0001:**
[figure not shown]
Summary of study schedule (SPIRIT 2013 figure).^15^, ^16^

In the case that a subject presents with onychomycosis affecting both halluces, then both halluces will be measured and sampled for mycology testing as described above. If both halluces test positive for dermatophytes, then the hallux with the larger affected nail surface area within the inclusion limit will be designated as the treatment target. If a dermatophyte is not detected at screening, then a repeat sample may be taken during a subsequent visit; in the case that a repeat sample tests positive for dermatophyte, then the subject will qualify for the study. Additionally, up to three other toenails may be designated as ‘non‐target’ toenails at the investigator's discretion and will receive the same treatment.

### Study intervention

2.2

On day 0, patients will be randomized (1:1:1) to one of three treatment groups (Groups A–C) based on a computer‐generated randomisation schedule generated prior to the start of the study (Figure 1). Group A will undergo nine treatment sessions, which includes the first session at day zero followed by four weekly sessions then four monthly sessions. Group B will undergo 7 treatment sessions, which includes the first session at day 0 followed by sessions every 2 weeks for 2 sessions then 4 monthly sessions. Group C will undergo 12 treatment sessions, which includes the first session at day 0 followed by sessions every 2 weeks.

Non‐responders at the end of the month 6 visit (day 168) or month 9 visit (day 252) as judged by the US FDA recommended endpoint (i.e., “temporary increase of clear nail”) will be given the option to undergo retreatment once per month for 3 months up to month 9 or month 12, respectively (Figure 1).^13^ Subjects who do not wish to undergo retreatment will be asked to return for month 9 and month 12 visits.

Tinea pedis is a common co‐infection seen in onychomycosis patients^17^; in this study, patients presenting with concomitant tinea pedis, at the investigator's discretion, may be provided with topical antifungal agents for treating affected skin areas. Toenails will be strictly avoided. No local anaesthetic, petroleum jelly nor metallic‐based topical treatments (e.g., aluminium chloride, silver nitrate) are to be used in the toenail areas during this study. Concomitant use of oral antifungal agents is not permitted.

### Treatment procedures

2.3

At enrolment, one affected hallux will be designated as the treatment target; up to 3 additional ‘non‐target’ toenails may also receive treatment. Prior to treatment, all visual and photographic assessments will be performed, in addition to sampling for mycology testing, as per the study schedule (Figure 1).

During each treatment session, toenails will be prepared by the clinician. Nails will be soaked in warm water for a minimum of 5 min to aid hydration and microwave energy absorption thereby generating heat in the nail plate and nail bed; then they will be cleaned with an antiseptic solution and allowed to dry. Microwave energy will be applied locally at a pre‐specified dose of 7–9 W for up to 3 s (i.e., one “burst”); treatment may be initiated at 9 W for up to 3 s with further adjustments of power and time settings depending on patient tolerability. Up to 5 additional bursts, spaced approximately 5‐s apart and subject to patient tolerability, may be administered in the same location and then repeated at a new location to ensure complete coverage of the nail surface. The affected nail area for treatment is chosen by the clinician administering the microwave energy and is concentrated on the proximal margin of discolouration and then distally as needed. The dose, duration and number of repetitions from each session will be recorded.

Investigators will follow the operation manual of the microwave device (Swift^®^ System, Emblation Ltd.). A new disposable tip will be fitted to the applicator probe used during each treatment session of up to 15 min from the first delivery of microwave energy. Ambient operating temperature should be between 10 and 30°C.

